##### Sociodemographic variables

Sociodemographic variables included are age, gender, cultural-ethnic background, education status, living situation (e.g., alone, with a spouse and/or children, in a group, with parents), type of housing, work/education/daytime activities (i.e. societal participation) and family situation.^1^

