##### Safety & discrimination: discrimination

The Dutch translation of the scale for daily discrimination of the National Survey of “Midlife Development in the United States” [60, 61] will be used to assess personal experiences with discrimination. The scale includes 7 types of discrimination, that are assessed with 9 Likert-type items (e.g., *How often do you experience being treated less politely than other people)* with answer categories ranging from 1 = *often* to 4 = *never*. Levels of daily discrimination are measured according to a total score of the recoded 9 items with higher scores indicating higher perceived discrimination. The internal consistency of the discrimination scale is high (alpha = .97) [61].

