### Statistical methods

All cross-sectional socio-demographic data from both baseline and follow-up measurements will be reported in terms of percentages, means with standard deviations, and quartiles. In addition, all study measures (from the instruments administered and from the registry data) will be analyzed descriptively to provide estimates of the relevant proportions within our study population with respect to these variables as (partial) answers to research questions 2, 4 and 5.

In addition, to provide information on the association between experienced need, and the primary outcome variables (research question 1), data collected at baseline will be analyzed using multivariate regression with recovery, societal participation and quality of life as separate dependent variables and total scores on the CANSAS (i.e. number of unmet needs for care), discrimination scale, stigma scale and victimization as independent (predictor) variables. Any potential mediating effects on the associations between predictors and outcomes variables will be investigated by adding age, sex, psychiatric symptoms (BPRS-E), harmful/dependent alcohol and/or drug use (AUDIT and DUDIT respectively), physical health (RAND SF-36) and city-districts as covariates in these analyses.

To answer research question 2, relationships between the outcome measures and distinct CANSAS items, registry data concerning the care process (i.e. treatment compliance, therapeutic alliance, frequency and timeliness of care consults and self-reported support for social problems) from mental health institutions and support/welfare organizations will mainly be reported in terms of percentages and, for obvious comparisons between groups, using regression models and chi-squared tests. Their associated proportion of variance explained Nagelkerke’s R^2^, Phi for 2 × 2 tables and Cramer’s V for larger than 2 × 2 tables will be reported. Phi and Cramer’s V will be interpreted as indicating no or very weak (> 0), weak (>.05), moderate (>.10), strong (>.15) or very strong (>.25) association between variables [93]. Eta-squared and Cohen’s D will be interpreted as very small (0–.19), small (.20–. 49), moderate (.50–.79), large (.80–1.20), very large (1.20–1.99) or huge (2.0) [94].

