Research question 3 will be analyzed using data from the baseline and follow-up measurement by means of generalized linear mixed models with repeated measurements of recovery, quality of life and societal participation as dependent variables. The time between both measures will be included as a within-subjects factor. The same set of predictor variables as mentioned above will be treated as time-dependent independent variables. Additionally, the total score on Brugha’s life-events questionnaire will be included as a potential mediator to assess the effect of having experienced adverse life-events in the time period between baseline and follow-up on the associations between predictor and outcome variables. All variables will be checked for potential outliers. Missing values will be dealt with appropriately. Participants with > 80% missing values on all items will be deleted from the final dataset. For most measures, descriptive analyses will be carried out and the proportion of missing values will be reported for each variable of interest. In subsequent statistical analyses, values missing at (completely) random (i.e. MAR and MCAR) will be deleted pair wise. Values that are not missing at random (NMAR) will be imputed with either the mean, median or using multiple imputation, whichever is most appropriate. Concerning outcome measures that are a sum score of items, instructions from the instrument developers will be followed (e.g., impute missing values with the mean value of the non-missing items and calculate a sum score only if < 10% of items are missing).

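### The fixed covariate list for the primary-outcome regressions omits cultural-ethnic background and education, both collected, and labels confounders as mediators, so residual confounding of unknown size is possible

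*Protocol article*

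**What the plan says.** The baseline analysis in Statistical methods is a "multivariate regression with recovery, societal participation and quality of life as separate dependent variables". The predictors are "total scores on the CANSAS (i.e. number of unmet needs for care), discrimination scale, stigma scale and victimization as independent (predictor) variables".

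The further covariates come in one sentence, which opens "Any potential mediating effects on the associations between predictors and outcomes variables will be investigated by adding age, sex" and gives in full the list "adding age, sex, psychiatric symptoms (BPRS-E), harmful/dependent alcohol and/or drug use (AUDIT and DUDIT respectively), physical health (RAND SF-36) and city-districts as covariates". The list carries no words such as 'for example', and nothing in it is deferred to another document.

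Under Sociodemographic variables the article states: "Sociodemographic variables included are age, gender, cultural-ethnic background, education status, living situation". So both cultural-ethnic background and education will be in the dataset. The same sentence goes on to treat "work/education/daytime activities (i.e. societal participation") as one block, which places current education inside an outcome domain.

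For the two-wave mixed models the article says: "The same set of predictor variables as mentioned above will be treated as time-dependent independent variables". The life-events score is added there as a further potential mediator. Neither cultural-ethnic background nor education is added.

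**The concern.** A variable that affects both a predictor and an outcome biases their association if it is left out. Cultural-ethnic background is a plausible case. The discrimination scale asks about everyday treatment in general ("How often do you experience being treated less politely than other people") and does not tie it to mental illness, as the separate stigma scale does. Its score may therefore reflect ethnic as well as illness-related discrimination. On the outcome side, the primary measures include formal work or daytime activities and the Social Exclusion Index, which has material deprivation and access to social rights among its parts. These could differ by ethnic background for reasons other than discrimination as measured. Attained education could similarly be related to need, victimization and participation.

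The labelling adds to the problem. All covariates are introduced as possible mediators. If fixed characteristics enter in the same step as symptoms, substance use and physical health, a change in a predictor's coefficient cannot be read as either removal of confounding or mediation. At stake is whether a coefficient for discrimination, victimization or unmet need reflects that predictor or, in part, a background difference that the study has measured and not used.

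**Working it through.** **1. Collected against adjusted for.**

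| Variable | Collected | In the covariate list | Can it mediate the effect of discrimination or unmet need? |
|---|---|---|---|
| Age, sex | yes | yes | no |
| City-district | yes | yes | not plausibly |
| Symptoms, alcohol/drug use, physical health | yes | yes | yes |
| Cultural-ethnic background | yes | **no** | no |
| Education status | yes | **no** | attained level possibly; current enrolment overlaps the outcome |

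The list mixes two kinds of variable under the mediator label and leaves out one clearly antecedent variable.

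**2. Does district stand in for the missing variables?** The Setting section selects two quarters in each of 7 residential districts, 14 quarters in all. The Bias section argues that socio-economic and background characteristics differ between quarters more than within them. A district term cannot separate the two quarters inside a district, so on the article's own reasoning it is a coarse proxy. No area term replaces the individual data.

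**3. Planned sample (Participants section).** Cohort size times expected response:
- in care: 1739 × 0.33 = 573.9
- not in care: 820 × 0.20 = 164.0
- LZA: 157 × 0.50 = 78.5
- total: 816.4, consistent with the stated figure of approximately 800.

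The approximate standard error of a standardised slope is 1/√800 = 0.035. Correlated predictors would make it larger.

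**4. Possible size of the bias.** The document gives no association of ethnic background or education with any predictor or outcome, so every input here is an assumption. Let y = b·x + g·z with all variables standardised and r the correlation of x and z. Omitting z shifts the slope of x from b to b + r·g.

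| r = g | bias r·g | bias ÷ 0.035 | share of an assumed true slope of 0.20 |
|---|---|---|---|
| 0 | 0 | 0 | 0% |
| 0.1 | 0.01 | 0.3 | 5% |
| 0.2 | 0.04 | 1.1 | 20% |
| 0.3 | 0.09 | 2.6 | 45% |

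For a two-group z with minority share p, the equivalent is p(1−p)·dX·dY, where dX and dY are the group differences in predictor and outcome in SD units. With p = 0.4, dX = 0.3, dY = 0.2: 0.24 × 0.06 = 0.014. With p = 0.5, dX = 0.6, dY = 0.5: 0.25 × 0.30 = 0.075. Both lie inside the range above. The sign of the bias depends on the signs of r and g.

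**5. Limits of step 4.** The formula is for one predictor and a linear outcome. The planned model has four related predictors plus symptoms, substance use, physical health and district, which may absorb part of the bias. The formula does not carry over directly to the yes/no work/daytime-activities outcome. It illustrates one omitted variable with one predictor and does not estimate the bias for each of the four.

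**The case against.** The strongest reply is that the sentence announces an examination of mediation within an association analysis and does not define a confounder set. Ethnic background cannot mediate discrimination, so on that reading its absence is no contradiction, and a condensed article may leave further adjustment to the full plan. The first part is fair as to the label. But age, sex and district are no mediators either, so the list already works as an adjustment set. The article also fixes it explicitly, so this is a choice it makes and not a detail it leaves open.

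The second reply concerns education, and it stands. The stigma scale includes an item on discrimination in education because of mental health problems, so education can be a consequence of earlier stigma or discrimination. Current education also belongs to the participation domain. Education therefore cannot simply be treated as a common cause that precedes the predictors.

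A reader might also infer more than the document supports:
- That the associations *are* confounded. No association with ethnic background or education is reported, so this is a risk, and zero bias is within the range.
- That false-positive rates are substantially raised for all the predictors. Such a figure would rest wholly on assumed inputs for one pair of variables in a single-predictor linear model, with nothing computed for education, victimization or unmet need.
- That these are the study's primary regressions. The article calls the outcomes primary, and the abstract defines them as changes over time. The regression quoted is cross-sectional and described as informing associations.

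**Conclusion.** The point holds as a weakness in a fixed covariate list. Two collected background variables are left out of the regressions of the primary outcomes, and variables that can only be confounders are called mediators alongside variables that might be mediators. The case is firm for cultural-ethnic background, which precedes the predictors and plausibly bears on a discrimination score not tied to illness. It is weaker for education, which needs a definition and a separate model.

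The consequence is possible residual confounding of unknown size and direction: illustratively 0 to 0.09 SD per SD in absolute value, about 0 to 2.6 standard errors at 800 participants, under assumed links of 0 to 0.3. It bears most on discrimination and possibly on victimization and unmet need. A larger sample would not remove it.

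**What to change.** In Statistical methods, split the covariates into two named sets:
- **Confounders:** age, sex, city-district and cultural-ethnic background.
- **Possible mediators:** symptoms (BPRS-E), alcohol and drug use, physical health, added in a separate later step.

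Carry cultural-ethnic background into the two-wave mixed models as a time-fixed covariate. Add highest attained education level in a further model, stating that current enrolment is not used because it overlaps the participation outcome. For each of the four outcome indicators, report every predictor's coefficient with and without these variables.

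The cost is a few sentences of text and a few degrees of freedom out of about 800, with no new data. The one statistical downside is possible over-adjustment if attained education was itself shaped by earlier illness-related discrimination. Keeping education in its own model, with coefficients side by side, would show how far the results depend on it.

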**Methods:**

A cohort design will be used. A representative sample of community-dwelling adults with an SMI, including those in care (*n* = 650) and not in care (*n* = 150), will be followed over time. During a two-year time period, participants will be interviewed twice using a wide-ranging set of validated instruments. Interview data will be matched with administrative data about the care process, as retrieved from their patient files. Primary outcomes are changes over time in recovery, societal participation and quality of life, controlled for the occurrence of adverse life-events during follow-up. Additionally, prevalence estimates of and associations between social functioning, safety and discrimination, substance use and health indicators will be investigated.

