With respect to the in-care and not-in-care cohorts, their relative proportions within the total SMI-population in Amsterdam are approximately 76 and 24%, respectively [30]. Furthermore, around 90% of both groups lives independently (i.e. community dwelling). In-care participants will be recruited at the two largest mental health care providers in Amsterdam, Arkin and GGZ inGeest. Together, these organizations are estimated to provide care/treatment to two thirds of the total in-care population of people with an SMI in Amsterdam [39]. The remaining 33% of the in-care SMI-population, those who receive mental health care from one of several other (small) providers, will not be included as we expect to obtain a representative sample of the in-care population from the selected service providers. Moreover, recruiting participants at numerous care providers would require a disproportional effort and is therefore considered unfeasible. The ‘not-in-care’ participants will be recruited at a variety of social welfare and social support organizations in Amsterdam, including organizations that target the homeless (e.g., HVO-Querido, Leger des Heils, Cordaan, Volksbond). In this group, the SMI-criteria will be assessed during the interview.

As such, on the basis of 1) the assumed average SMI prevalence of 1.6% among the adult population of the selected quarters (237,157 * 1,6% = 3795 people), and 2) the proportion of adults with an SMI who are registered as a mental health care patient (76%, *n* = 2884), and 3) of whom at one of the two main mental health care providers in the city (66%, *n* = 1903) and 4) the proportion within this group who live independently (i.e. community dwelling) (90%), the in-care cohort is estimated to consist of 1739 adults with an SMI. On the basis of the aforementioned proportions, the not-in-care cohort is estimated to consist of 820 people. The LZA-cohort potentially consists of 157 former LZA-participants who gave permission to be re-approached. Based on expected response rates of 33% in the in-care cohort, 20% in the not-in-care cohort and 50% in the LZA-cohort, the study sample will consist of approximately 800 participants. Figure 1 presents a flowchart depicting the composition of the study population.

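### The fixed verbal scale for Phi and Cramer's V ignores table size, N and the test result, so chance alone often earns a label: weak at full sample, moderate or stronger if tables are run at n = 150

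*Protocol article*

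**What the plan says.** Under Statistical methods, research question 2 relates the outcome measures to individual CANSAS items and to care-process data. Results are to be given chiefly as percentages and, for some group comparisons, "using regression models and chi-squared tests". As effect sizes, "Phi for 2 × 2 tables and Cramer’s V for larger than 2 × 2 tables will be reported". Both are then read on one verbal scale, taken from a cited source: "no or very weak (> 0), weak (>.05), moderate (>.10), strong (>.15) or very strong (>.25) association between variables".

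Nothing in the section makes the wording depend on the number of categories, the number of participants, the test result or an interval, and no bias correction is mentioned.

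On size, the Exclusion criteria section concludes that "the study sample will consist of approximately 800 participants". The Abstract splits this into 650 in care and 150 not in care.

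**The concern.** Cramer's V cannot be negative, and unless the sample is very large its value under independence is clearly above zero. In an r x c table of N people with no association, the expected value of V² is about (r−1)(c−1) / [N × min(r−1, c−1)]. The noise level therefore rises as N falls and, for a two-level outcome, as the other variable gains categories. A scale that starts at .05 and is blind to both will attach words of association to chance findings.

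Research question 2 asks which needs matter most for recovery and participation. With 25 CANSAS items, a reader scanning the labels could take unrelated needs for relevant ones. The same word would also carry different evidence in cohorts of different size.

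**Working it through.** **Sample size, from the plan's own inputs.** The Exclusion criteria section gives frames of 1739 (in care), 820 (not in care) and 157 (LZA), with response rates of 33%, 20% and 50%:

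1739 × 0.33 + 820 × 0.20 + 157 × 0.50 = 573.9 + 164.0 + 78.5 = 816.4.

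This agrees with about 800. In care plus LZA is 652, against the stated 650. Not in care is 164, against 150.

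**Table implied by the plan.** A CANSAS item has three levels (Health: perceived needs for care). The one categorical primary indicator, formal work or daytime activities, is yes/no (Primary study outcomes). This gives a 2 x 3 table with df = 2 and min(r−1, c−1) = 1.

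**Formula.** Under independence N × min(r−1, c−1) × V² is approximately chi-square with (r−1)(c−1) df, so P(V > t) = P(χ² > N × min × t²). For df = 2 this is exp(−N t²/2).

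- N = 800: t = .05 gives exp(−1) = 0.368; t = .10 gives exp(−4) = 0.018.
- N = 650: t = .05 gives exp(−0.8125) = 0.444; t = .10 gives exp(−3.25) = 0.039; t = .15 gives exp(−7.3125) = 0.0007.
- n = 150: t = .10 gives exp(−0.75) = 0.472; t = .15 gives exp(−1.6875) = 0.185.

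Chance of each label or a higher one when there is no association:

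| Table | N | weak (>.05) | moderate (>.10) | strong (>.15) | very strong (>.25) |
|---|---|---|---|---|---|
| 2 x 2 | 800 | 15.7% | 0.5% | 0.0% | 0.0% |
| 2 x 3 | 800 | 36.8% | 1.8% | 0.01% | 0.0% |
| 2 x 2 | 650 | 20.2% | 1.1% | 0.01% | 0.0% |
| 2 x 3 | 650 | 44.4% | 3.9% | 0.07% | 0.0% |
| 2 x 2 | 150 | 54.0% | 22.1% | 6.6% | 0.2% |
| 2 x 3 | 150 | 82.9% | 47.2% | 18.5% | 0.9% |

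Simulation of 40,000 tables per setting, with assumed margins, agreed within about 0.01.

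**Per 25 CANSAS items, all unrelated to the outcome.** At N = 800 the expected number labelled at least *weak* is 25 × 0.368 = 9.2, and at least *moderate* 25 × 0.018 = 0.5. At n = 150 the expected numbers are 25 × 0.472 = 11.8 at least *moderate* and 25 × 0.185 = 4.6 at least *strong*. With n = 164 instead of 150, the two rates are exp(−0.82) = 44% and exp(−1.845) = 16%.

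**Label against test (alpha .05 assumed; the protocol states none).** For df = 2 the critical chi-square is 5.99, so p < .05 needs V above √(5.99/N): .087 at N = 800, .096 at N = 650 and .200 at n = 150. At n = 150 the whole *moderate* band and half of the *strong* band (.15 to .20 of .15 to .25) are therefore non-significant. At N = 650 everything labelled *moderate* is significant.

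**Effect of possible remedies (simulated).** For the 2 x 3 table at n = 150, bias-corrected V lowers the noise rate for *moderate* or higher from 48% to 18%, and for *strong* or higher from 19% to 7%. Giving a label only when p < .05 holds false labels at about 5% in every setting.

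**The case against.** The strongest reply is that V is planned as the companion of a chi-squared test. For a given table the two carry the same information, so a reader who looks at the p-value would discount most of these labels. This reduces the harm but does not remove it: the stated rule assigns the word whatever the test shows, and at n = 150 the word and the test disagree over a wide range.

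Other points on this side stand and limit the claim:

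- A reader might infer that noise will be called moderate to strong throughout the study. The figures do not support this: at N = 650 to 800, 2 x 2 and 2 x 3 tables pass .10 by chance in 0.5% to 4% and .15 in under 0.1%.
- The protocol does not say that V will be computed within the not-in-care cohort, nor that labels will be compared between cohorts. It does distinguish the cohorts and foresees group comparisons, so such tables are plausible, but they are an assumption.
- Larger noise rates arise with many categories: a seven-category variable against a yes/no outcome passes .10 in 24% at N = 800, and passes .15 in 76% at n = 150. However, city-districts are named only as regression covariates, quarters only as a sampling level, and the category counts of the registry variables are not given. These rates illustrate the mechanism and do not describe a planned table.
- It would be wrong to say that research question 2 is answered mainly through these labels. Percentages are the main form of report, and three of the four primary indicators are total scores, to which Phi and V do not apply unless categorised.

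A bias correction or interval could also be left to a fuller document. The labelling rule itself, however, is fixed in this text.

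**Conclusion.** The point holds in a limited form. The scale ignores degrees of freedom, N and the test, so it can name chance as association. In the tables the protocol clearly implies, at full sample, the error is almost wholly confined to the *weak* label (16% to 44% of unrelated tables). It becomes serious only in small subsets: at n = 150, noise reaches at least *moderate* in 22% of 2 x 2 and 47% of 2 x 3 tables, and at least *strong* in 7% and 18%. With a yes/no outcome, more categories raise these rates further.

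The figures assume independent observations, complete data, cell counts large enough for the chi-square approximation, alpha of .05 where the test is mentioned and, for n = 150, that tables are run within that cohort. The reading that moderate-to-strong noise is a general feature of the study is not supported. This is a cheap improvement to a stated rule; it does not put the primary analyses in doubt.

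**What to change.** Amend the labelling sentence in Statistical methods as follows:

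- Report bias-corrected Cramer's V (and phi) with a 95% confidence interval beside the chi-squared p-value.
- Give a verbal label only when the planned test rejects independence at a stated alpha (.05 assumed here), or when the interval excludes no association. Choose one criterion in advance. If the interval is used, it needs a method that can return zero as its lower limit, for example one based on the noncentral chi-square.
- Otherwise write that an association was not shown.
- Do not compare verbal labels between cohorts of different size; compare estimates with their intervals.

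Bias correction without the second step is not enough, as the 18% that remains at n = 150 shows. Even with it, 25 unrelated items would yield about 25 × 0.05 = 1.25 false labels, so the number of tables examined should be stated with the results.

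The cost is a sentence or two, with no new data. Fewer associations will receive a label, especially in the small cohort, where a modest true association may be reported as not shown.

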##### Subjective appraisal & recovery: personal recovery

The Dutch national recovery scale (in Dutch “Nationale Herstelschaal”) [77], an adaptation of the Questionnaire about the Process of Recovery (QPR) [78], will be used to assess specifically personal recovery. This instrument measures personal recovery on the basis of 26 Likert-type items ranging from 1 = *strongly disagree* to 5 = *strongly agree.* Examples of items are *I feel good about myself*, *My life has a purpose*, *I can manage to actively engage life* and *I have trust in others*. A total score can be computed with a maximum of 4 missing answers and scores range from 26 to 100. Higher scores indicate higher personal recovery. The NHS has been shown to be a user-friendly, reliable and valid instrument [77].

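### Cohen's d bands are applied to eta-squared, which they cannot fit, and the stated 26 to 100 range of the primary recovery score does not match its own items and scoring

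*Protocol article*

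**What the plan says.** **Effect-size labels.** The Statistical methods section states: "Eta-squared and Cohen’s D will be interpreted as very small (0–.19), small" from .20 to .49, with *moderate* from .50 to .79, *large* from .80 to 1.20, *very large* from 1.20 to 1.99, and *huge* at 2.0. The sentence just before it gives two other indices a scale of their own: "Phi and Cramer’s V will be interpreted as indicating no or very weak (> 0), weak (>.05), moderate (>.10), strong (>.15) or very strong (>.25").

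**Recovery score.** The section on personal recovery says that the National Recovery Scale "measures personal recovery on the basis of 26 Likert-type items ranging from 1" (strong disagreement) to 5 (strong agreement). It then says: "A total score can be computed with a maximum of 4 missing answers and scores range from 26 to 100". Table 1 also lists 26 items. Primary study outcomes makes the total of this scale the recovery outcome.

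**Data checks.** On screening of values, Statistical methods says only: "All variables will be checked for potential outliers".

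**The concern.** Eta-squared is the share of variance explained and lies between 0 and 1. Cohen's d is a difference in standard deviation units and has no upper limit. One set of cut-offs running to 2.0 cannot serve both. Anyone who follows the rule would call a difference *large* when reporting d and *very small* when reporting eta-squared. The study is largely descriptive and associational, so these words are part of how strength of association would reach the reader.

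The recovery score raises a different matter, namely whether a primary outcome is described correctly. The lower limit fits a plain sum of the items and the upper limit does not. A reader could not tell what a given total means relative to the top of the scale, and whoever prepares the data would have the wrong limits to hand.

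**Working it through.** **1. Effect-size bands**

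Inputs: the shared bands from Statistical methods, and the planned group sizes of 650 in care and 150 not in care from the Abstract. The bands print 1.20 in both *large* and *very large*; here it is counted as *very large*.

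For two groups with share p in one of them, eta-squared = d² / (d² + 1/(p(1−p))).

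- Equal groups: p = 0.5, so 1/(p(1−p)) = 4.
- 650 versus 150: p = 650/800 = 0.8125, so 1/(0.8125 × 0.1875) = 6.56.

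| d | Label as d | Eta-squared, equal groups | Label | Eta-squared, 650:150 | Label |
|---|---|---|---|---|---|
| 0.2 | small | 0.010 | very small | 0.006 | very small |
| 0.5 | moderate | 0.059 | very small | 0.037 | very small |
| 0.8 | large | 0.138 | very small | 0.089 | very small |
| 1.0 | large | 0.200 | small | 0.132 | very small |
| 1.2 | very large | 0.265 | small | 0.180 | very small |
| 2.0 | huge | 0.500 | moderate | 0.379 | small |

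Working back from the cut-offs:

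- Eta-squared 0.19, equal groups: d = 2 × √(0.19/0.81) = 0.97. Everything below this is *very small*.
- Eta-squared 0.20, equal groups: d = 2 × √(0.20/0.80) = 1.0, where *small* begins.
- Eta-squared 0.20, 650:150: d = √(0.25 × 6.56) = 1.28, where *small* begins.
- Eta-squared 0.80, equal groups: d = 2 × √(0.80/0.20) = 4.0, where *large* begins.
- Eta-squared of 1.20 or 2.0 is impossible, so *very large* and *huge* are empty.

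**2. Range of the recovery score**

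Inputs: 26 items (personal recovery section and Table 1), each scored 1 to 5 (personal recovery section).

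- Minimum: 26 × 1 = 26. This matches the stated lower limit.
- Maximum: 26 × 5 = 130. This does not match the stated 100.

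Other readings do not reproduce 26 to 100 either:

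- Four items missing with no imputation: 22 × 1 = 22 to 22 × 5 = 110.
- 26 items scored 1 to 4: 26 to 104.
- 26 items scored 0 to 4: 0 to 104.
- 25 items scored 1 to 4: 25 to 100.
- 20 items scored 1 to 5: 20 to 100.
- Sum expressed as a percentage of the maximum: 26/130 = 20% to 100%.

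The article describes no rescaling.

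**The case against.** The strongest reply is that little depends on either sentence. For research question 2 the article names percentages, regression models and chi-squared tests, with Nagelkerke's R², phi and Cramer's V. Eta-squared and d appear only in the sentence on interpretation, and no named analysis is said to produce them. The recovery outcome is the computed total, and Statistical methods defers to the instrument developers for sum scores, so a misprinted maximum changes no one's score. This stands as a limit on impact. It does not rescue the bands, because the article commits to reading eta-squared by them.

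Four stronger readings are tempting, and the article does not support them:

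- *High scorers would be truncated or flagged.* Of the 104 steps between 26 and 130, 30 (29%) lie above 100. But the article sets no range check, no cap and no deletion rule; it mentions only a general check for outliers. The 29% is a share of possible score steps, not of participants, and no score distribution is given.
- *The maximum is the figure in error.* The article shows only that item count, item scoring and maximum do not agree. It does not show which is wrong.
- *Every large effect becomes very small.* With equal groups this holds up to about d = 0.97. From d = 1.0 to just under 1.2 the label is *small*. Only with the 650:150 split does the whole *large* band for d fall to *very small*.
- *Phi adds a further contradiction.* A phi of 0.26 is *very strong*, while the corresponding d of about 0.54 is *moderate*. That gap comes from two separate benchmark sets and would remain after the eta-squared bands are corrected. The article does not say that all these indices would be reported for one association. The phi sentence shows only that the article already gives different indices different scales.

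**Conclusion.** Both errors are in the current text and follow from its own figures.

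The shared bands are wrong for eta-squared whatever the data show, because two of the six bands lie beyond its maximum. The size of the mislabelling rests on the two-group formula. Under it, a *large* d of 0.8 becomes *very small* both with equal groups (0.138) and with 650 versus 150 (0.089).

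The stated recovery range is inconsistent with 26 items scored 1 to 5. If that scoring is right, the range is 26 to 130. That is conditional, because the instrument's scoring instructions are not in the article.

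The consequence is limited to the labelling of results and the description of a primary outcome. No test, estimate, model or sample-size figure changes.

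**What to change.** **Effect sizes.** Keep the stated bands for Cohen's d only. Then choose one of two options:

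- Give eta-squared its own benchmarks, for example 0.01, 0.06 and 0.14, with 0.26 and 0.50 for the upper bands. Describe them as equal-group equivalents of the d cut-offs 0.2, 0.5, 0.8, 1.2 and 2.0. They do not carry over to unequal groups: at 650:150, d = 0.2, 0.5, 0.8 and 1.2 give 0.006, 0.037, 0.089 and 0.180, each one label too low. The two-group formula also does not apply to comparisons of more than two groups, such as city districts.
- For two-group comparisons, report and label d only. This avoids the dependence on group sizes.

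**Recovery score.** Check item count, item scoring and maximum against the instrument's scoring instructions, and correct whichever is wrong. If the stated scoring is right, write 26 to 130; if scores are transformed, state the rescaling. Do this before scores are checked or described.

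**Cost.** About two sentences of text, with no new data and no change to any analysis.
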